#### Data collection tools

The household survey focuses on question (1) and collects information on the nutritional and health status of each selected child, as well as general information on their household (including socio-economics, food security variables). The health facility survey focuses on questions (2), (3) and (4). To get information on malnutrition recovery rates, a total of 24 individual clinical files randomly selected among the files of all children below five years old enrolled in the MAM care program (12 files) and in the SAM care program (12 files) during the last six months are transcribed. In addition, organizational aspects of the HCs as well as of the nutrition services are recorded through interviews to managers. To assess the quality of services, we combine two techniques: patient-provider observations carried out on six paediatric consultations (performed by a maximum of two HWs) and exit interviews at the end of each of these observed consultations, in order to get information on the satisfaction level as well as to record anthropometrics of the children. Finally, to assess knowledge of the observed HWs, we use vignettes to measure the practical knowledge on different tasks to perform: a pattern of consultation is proposed and the health worker can ask all the questions (related to history and physical exams) necessary to arrive at a diagnosis and propose a treatment. Three vignettes are administered to every health worker observed in consultation.

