## General objectives and research questions

The overarching objective of our research is to assess the effects of the introduction of criteria focusing on malnutrition prevention and care activities in the existing PBF system. Main research questions at 1) population and 2) HC levels are:Does the introduction of criteria focusing on malnutrition prevention and care activities in the existing PBF system result in a reduction in acute and chronic malnutrition rates in the community?Does the introduction of criteria focusing on malnutrition prevention and care activities in the existing PBF program result in better outcomes at the facility level, i.e. in better management of malnutrition cases (better recovery rates, shorter periods of treatment, etc.)?

In addition, the research incorporates two sub-questions which will allow identifying the possible causes of the success or any disappointing outcome, including unintended side-effects: Table 33)What are the transmission mechanisms induced by the introduction of criteria focusing on malnutrition prevention and care activities in the existing PBF program?4)What are the reasons for the success or failure of PBF on nutrition activities?

**Table 3 Tab3:** Main outcomes for the impact evaluation

Level	Outcomes
Population	- Prevalence of acute malnutrition (defined as WHZ < -2 or MUAC < 125 mm) and of stunting (defined as HAZ < -2) among children aged 6-23 months - WHZ, HAZ and MUAC among children aged 6-23 months
Health Centre	- Recovery rates from MAM and SAM cases of children below five years old - Duration of treatment of MAM and SAM cases of children below five years old

Notes: HAZ stands for Height-for-Age Z-score; MAM for Moderate Acute Malnutrition; MUAC for Mid-Upper Arm Circumference; SAM for Severe Acute Malnutrition; and WHZ for Weight-for-Height Z-score

In addition to these questions, the data collection has been designed in such a way to allow assessment of equity and efficiency of the intervention, potential externalities on other outcomes, and systemic spill-over effects, including possible demand for professional training by the health facilities. These aspects are not covered in this protocol paper.

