The sample size of clinical files within the HC survey was computed on the smallest difference in the main outcome that could be considered of public health significance in intervention centres. Assuming that the intervention will result in increasing the recovery rate of acute malnutrition in children under five years from 80 % to 90 %, for an α-error of 5 %, a power of 80 % and an inter-cluster correlation (ICC) of 0.15 [25], a minimum of 12 clinical files per HC and per nutrition service (MAM and SAM rehabilitation services) were needed, among all children having been registered in the six previous months [26].

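### Clinical files are sampled by registration in the six months up to the survey, so some episodes are still open, and the 12-file minimum has no reserve for them

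*Protocol article*

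**What the plan says.** The protocol article describes the file sample twice. Under Sample size and randomization, at least 12 files per health centre and per service are drawn "among all children having been registered in the six previous months". Under the quantitative Data collection tools, the 12 MAM files are "randomly selected among the files of all children below five years old enrolled in the MAM care program". The 12 SAM files are taken in the same way, and one six-month period ending at the survey applies to both services. Both descriptions define the frame by entry. Neither requires that the child has left the programme, sets a minimum time since admission, or leaves out the latest admissions.

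Table 3 lists two kinds of main outcome at health-centre level: "Recovery rates from MAM and SAM cases of children below five years old" and "Duration of treatment of MAM and SAM cases of children below five years old". The file number is justified by "increasing the recovery rate of acute malnutrition in children under five years from 80 % to 90" per cent, with α 5%, power 80% and "inter-cluster correlation (ICC) of 0.15".

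The quantitative Analysis strategy plan gives recovery (yes/no) as an example of a categorical outcome for logistic or Poisson regression, and assigns continuous outcomes to mixed-effect regression. It does not mention open episodes or censoring.

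**The concern.** A child registered a week before the survey is eligible for the sample but has no outcome. This is a property of the stated sampling rule, not a gap in the record. A perfectly kept file for a child still in treatment contains neither a recovery result nor a final duration.

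Each simple way of handling such files has a cost. Leaving them out gives fewer than the 12 outcomes the calculation calls a minimum, and it selects short episodes, because long ones are more likely to be open at the survey. Keeping them understates recovery if they are not counted as recovered, and understates duration if they are cut at the survey date.

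MAM and SAM recovery and MAM and SAM duration are all drawn from these files. Randomisation does not guarantee that the distortion is equal in both arms, because the open share depends on how long treatment lasts, and shorter treatment is one of the effects the trial is looking for.

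**Working it through.** **Inputs from the protocol article.** Recovery 80% versus 90%; α 5% (sidedness not stated; two-sided reproduces the figure); power 80%; ICC 0.15; 45 centres per arm; 12 files per centre and service; a registration window of six months, taken as 26 weeks.

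**Assumptions, because the article gives no figure.** Even enrolment over the window; mean treatment of 6, 8, 10 or 12 weeks; for the duration bias, gamma-distributed durations with SD 3, 3, 4 and 4 weeks.

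**1. The plan's own figure.** Files per arm without clustering, with mean proportion 0.85:

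n = [1.96·√(2·0.85·0.15) + 0.842·√(0.8·0.2 + 0.9·0.1)]² / 0.10² = 199.

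With m files per centre, solve 45m = 199·[1 + (m − 1)·0.15]:

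m = 199·0.85 / (45 − 199·0.15) = 169.15 / 15.15 = 11.17, rounded up to 12.

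At m = 12 the design effect is 1 + 11·0.15 = 2.65. The effective number per arm is 45·12 / 2.65 = 203.8, and power is 80.9%. The stated 12 is therefore right, but its only slack is the rounding from 11.17. By contrast, the household sample was raised from 65 to 72 children per centre for missing data. No such allowance is stated for files.

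**2. Share of files still open.** With even enrolment over 26 weeks and mean duration D, the open share is D/26.

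**3. Power if open files are excluded.** Completed files m = 12·(1 − D/26); effective number = 45m / [1 + (m − 1)·0.15]; power from the same two-proportion formula.

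| Mean duration (assumed) | Open share | Completed files of 12 | Effective n per arm | Power |
|---|---|---|---|---|
| 6 weeks | 23% | 9.2 | 186 | 77% |
| 8 weeks | 31% | 8.3 | 178 | 76% |
| 10 weeks | 38% | 7.4 | 170 | 73% |
| 12 weeks | 46% | 6.5 | 160 | 71% |

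The loss is modest because, at an ICC of 0.15, extra files within a centre add little information.

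**4. Bias in duration.** Under the gamma assumption, the mean among completed episodes is about 6% to 10% below the true mean. If open files were instead kept with time to the survey date, the mean would be about 14% to 26% too short.

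**5. Does the bias cancel between arms?** Take true mean durations of 2 and 1.5 months (gamma, shape 4, assumed). Among completed files, the true difference of 0.5 month shrinks to about 0.38 month. The bias does not cancel even with equal enrolment in both arms.

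**6. Hypothetical worst case.** If open files were coded as not recovered, 80% versus 90% would become 62% versus 69% at 6 weeks (multiply by 1 − 6/26) and 43% versus 49% at 12 weeks (multiply by 1 − 12/26). Power at 12 files would be 37% and 19%. With equal true recovery of 80% and durations of 2 versus 1.5 months, the observed rates would be 0.80·(1 − 2/6) = 53% and 0.80·(1 − 1.5/6) = 60%, a spurious gain. The article states no such coding rule.

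**The case against.** The strongest reply is that handling of open files is ordinary analysis-plan detail, and that the full plan is not shown. This holds for the coding rule. A reader might infer from the yes/no recovery outcome that open episodes count as failures and that power collapses to 37% or lower. Nothing in the article says so, and those figures stand only as a hypothetical. The reply does not remove the point, because the entry-defined frame is stated twice and carries a cost whichever rule is chosen.

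Second, the power figures come from an unmatched, unadjusted comparison. The article pairs centres on recovery percentage and other parameters, plans to control for these, and uses both survey rounds. If that lowered the effective ICC to about 0.13, the 6-week case would return to 80% power: 45·9.23 / (1 + 8.23·0.13) = 201 effective files, against 199 needed. At 12 weeks the ICC would have to fall to about 0.08. The article gives no such reduction, so this is possible but not shown. The original 12 rests on the unadjusted calculation too.

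Third, some stronger readings go beyond the text:
- That duration would move in the wrong direction. This needs early default or death to count as short treatment, and the article does not define duration that way. The calculation among completed files shows attenuation, not reversal.
- That rising enrolment under PBF makes the open share differ by arm. This is neither documented nor quantified.
- That most files are unfinished. Under the assumptions above, 54% to 77% are complete.
- That duration is certain to be analysed as an ordinary continuous variable. The analysis section does not name it.

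Finally, the Discussion does warn that incomplete files may reduce power at health-centre level. It means poor record keeping, and its remedy is better filling in and archiving, which cannot supply an outcome for a child still in treatment.

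**Conclusion.** The point holds as a defect of the stated sampling rule. A frame of all registrations up to the survey must include open episodes at any non-zero treatment duration, and the 12-file minimum allows for none.

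The size cannot be fixed from the article. On assumed mean durations of 6 to 12 weeks and even enrolment, 23% to 46% of files would be open. Excluding them takes power from 80.9% to about 77% to 71% on the protocol's own unadjusted calculation, and shortens mean completed duration by about 6% to 10%. The loss of power is moderate. The more awkward consequence is a selection effect that depends on duration, an outcome the intervention is meant to change, so it need not be equal in the two arms. Recovery would be understated much more only under a coding rule that the plan does not contain.

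**What to change.** The follow-up survey still lay ahead when the article was written, so either of two changes could be made before it.

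1. Draw the 12 + 12 files from a six-month registration window that closes one maximum treatment length before the survey, so that sampled episodes are closed and the 12-file calculation applies as written.
2. To keep comparability with the baseline already collected, keep the present frame. In both rounds, analyse time from registration to recovery, censored at the survey date, with default, death and transfer as competing events. Report duration through that analysis, and restate the power for the expected number of completed files. Obtaining 12 completed files would need about 16 sampled files at a 23% open share (12 / 0.77) and 23 at 46% (12 / 0.54).

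Option 1 means retrieving slightly older files. If only the follow-up window moves, the rounds may no longer match in season or definition. Option 2 relies on exit dates in files that the article's Discussion reports as incomplete. Neither option affects patient care.

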#### Quality assurance plan and data management

During both survey rounds, lot quality assurance surveys are performed regularly by the field coordinator to assess accuracy of anthropometric data in the records. Most data are entered in “real-time”, and irregularities detected and corrected by the field coordinator on a continuous basis. Data entry is done with the use of an electronic device: Android smartphones with Open Data Kit software and the ONA internet data management platform have been chosen for this purpose^4^. The electronic data entry has the advantage of reducing risks of errors in recording the answers (thanks to automatic validity checks), and eliminating the need for double data entry from the paper to software transcription and to decrease considerably the time for transcription, estimated at 1,500 working days per survey round. Some questionnaires though need to be performed on paper (like the patient-provider consultation using an observation grid on paper): a double entry session is then organized to avoid any entry error.

#### Analysis strategy plan

First, some descriptive analysis are carried out in order to understand the main features of malnutrition management and of health services in general in Burundi at the HC level. Validation of the design was performed with the baseline survey data by comparing the treatment group with the control group.

Second, with both survey rounds’ data, the impact of the intervention will be assessed with multilevel statistical models with random effects at the HC level. Continuous dependent variables will be analysed in mixed-effect regression models, whereas categorical ones (e.g. recovery yes/no) will be analysed in logistic regression or Poisson regression models. At the population level, other factors of child malnutrition, such as household food security, socio-economic status, etc., will be controlled for. Interactions with season, child age and sex, stunting, and socio-economic parameters will be analysed. An equity analysis will also be performed in order to understand whether the intervention benefits more the poorer or richer households. At the HC level, other factors of child malnutrition recovery, such as for instance HC staff and CHWs knowledge and know-how, will be controlled for. Interactions with child age and sex, stunting and MUAC will be analysed.

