### The quantitative component

Our main questions (1) and (2) require quantified measures and the possibility to attribute variations in the outcome measures to the intervention. We have opted for a *cluster-randomized controlled evaluation design*, with health centres^2^ as the primary unit of sampling and *sous-collines*^3^ (sub-hills) as the secondary unit of sampling. The 90 selected nutrition HCs were allocated to either a control group (45) or a treatment group (45). For each household survey and around each selected HC, six *sous-collines* are randomly selected; and in each *sous-colline*, 12 households with at least one child aged 6–23 months are surveyed.

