#### Sample size and randomization

The sample size of the household surveys is computed on the smallest difference in the main outcome that can be considered of public health significance, i.e. a reduction of about 25 % in acute malnutrition prevalence in intervention centres as compared to control centres. Assuming that the intervention will result in decreasing the prevalence of MAM in children aged 6–23 months from 10 % to 7.5 % [3], and assuming that 65 children aged 6–23 months are to be surveyed in the catchment area of each HC, 90 HCs were needed to be randomized to either the intervention or control group, for an α-error of 5 % and a β-error of 20 %. The number of children per HC was increased to 72 to allow for missing or incomplete data, amounting to a total of 6,480 children aged 6–23 months over the 90 selected HCs. In total, a sample of 6,480 children were surveyed for the baseline, and, two years after the start of the program, another sample of 6,480 children aged 6–23 months will be surveyed.

Selection of HCs invited to participate in the study was done by simple randomization (computer-based random selection) among the 193 eligible HCs, i.e. HCs providing nutrition services (treatment of SAM and MAM). The 90 selected HCs have been paired on essential parameters of organization and functioning in relation to the outcomes (MAM rehabilitation activity, volume of activity, population in the catchment area, and percentage of recovery among malnourished children) as measured during the baseline survey. This will then be used to control for the potential confounding effect of these parameters. Within each of the 45 pairs, allocation to the intervention was done randomly through a lottery system organized by the MoH during a workshop in December 2014.

Simple randomization should be applied to select the households to be surveyed in the catchment area of the 90 HCs. However, such an approach was difficult logistically and could have turned out to be extremely resource-consuming. The chosen alternative option was to sample clusters of households, i.e. households living close to each other. Six clusters of 12 eligible households were selected at random from the whole catchment area of a given HC. This could be done without expanding the overall sample size given the quite high intra-class correlation considered for the sample computation.

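### The two-round impact model names only health-centre random effects; if that means an intercept alone, the standard error ignores clustering specific to each survey round

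*Protocol article*

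**What the plan says.** The Analysis strategy plan of the quantitative component says that, "with both survey rounds’ data", "the impact of the intervention will be assessed with multilevel statistical models with random effects at the HC level". The HC is the only level named. The section does not say whether the random effects are intercepts only, and it names no arm-by-round term.

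The sampling has a further level. Under The quantitative component, the sous-colline serves "as the secondary unit of sampling". The draw belongs to the survey round: "For each household survey and around each selected HC, six *sous-collines* are randomly selected", and in each of them "12 households with at least one child aged 6–23 months are surveyed". Sample size and randomization confirms this structure ("Six clusters of 12 eligible households were selected at random from the whole catchment area of a given HC") and states that at follow-up "another sample of 6,480 children aged 6–23 months will be surveyed". The household part is therefore a repeated cross-section. The HCs are the same in both rounds, but the children are new and sous-collines are selected for each round.

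**The concern.** An HC random intercept represents what an HC keeps across both rounds. It largely cancels when an effect is estimated from change within HCs. Two sources of correlation do not cancel:

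- **Sous-colline variance.** Children in the same sous-colline resemble each other, and the sous-collines are selected separately for each round.
- **HC-by-round variance.** An HC's prevalence may move between rounds for reasons of its own. The article reports political instability, delayed roll-out and donor withdrawal (Implementation; Discussion). These make such movement plausible, but the article puts no figure on it.

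A model with an HC intercept alone assigns both to independent child-level residuals. Confidence intervals for the main population question would then be too narrow, and the false-positive rate would exceed the planned 5%.

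**Working it through.** **Inputs from the article.** 45 HCs per arm; 6 sous-collines × 12 households = 72 children per HC and round; 10% versus 7.5% prevalence; 65 children per HC in the calculation; α 5% (two-sided assumed); power 80%. For clinical files: ICC 0.15 and 12 files per HC and service. No household ICC is given as a number.

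**The plan's own figure.** Comparing 10% with 7.5% needs 2,005 children per arm before clustering. The plan has 45 × 65 = 2,925. The implied design effect is 2,925 / 2,005 = 1.46, so the implied ICC is 0.459 / 64 ≈ 0.007. The 90 HCs are met at that ICC but cannot be confirmed without the missing value.

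**Standard error under an HC intercept alone.** Set the within-HC variance to 1. Let ρ_sc be the sous-colline share and ρ_hp the HC-by-round share. Then 72 × the variance of an HC-round mean, given the HC, is

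(1 − ρ_sc − ρ_hp) + 12ρ_sc + 72ρ_hp = 1 + 11ρ_sc + 71ρ_hp.

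The model takes this quantity to be about 1. For a difference between arms in change, the ratio of true to model standard error is therefore √(1 + 11ρ_sc + 71ρ_hp), and the type I error is 2(1 − Φ(1.96 / ratio)).

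| ρ_sc (assumed) | ρ_hp (assumed) | Variance ratio | SE ratio | Type I error |
|---|---|---|---|---|
| 0 | 0 | 1.00 | 1.00 | 5.0% |
| 0.01 | 0 | 1.11 | 1.05 | 6.3% |
| 0.02 | 0 | 1.22 | 1.10 | 7.6% |
| 0.05 | 0 | 1.55 | 1.24 | 11.5% |
| 0 | 0.0035 | 1.25 | 1.12 | 7.9% |
| 0.02 | 0.0035 | 1.47 | 1.21 | 10.6% |

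**Simulation.** Continuous outcome, 90 HCs, two rounds, 6 × 12 children, HC ICC 0.0072, 1,500 runs per setting, ρ_hp = 0:

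- ρ_sc = 0.02: empirical SD 0.0393 against a mean model SE of 0.0350; type I error 7.7%. It is 4.9% with a sous-colline effect added and 4.8% with an HC-by-round analysis.
- ρ_sc = 0.05: empirical SD 0.0447 against 0.0349; type I error 12.1%. It is 5.6% with a sous-colline effect and 5.1% with an HC-by-round analysis.
- ρ_sc = 0: type I error 5.8%, against 5.7% for both alternatives, so no understatement beyond simulation noise.

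**Common baseline mean.** If both arms share one baseline mean but the model still has only an HC intercept, the large-sample type I error is 6.8% at ρ_sc = 0.02 and 9.8% at 0.05 (HC ICC 0.0072). The problem shrinks but remains.

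**Clinical-file outcomes.** Files are not sampled through sous-collines, so only the HC-by-round part applies. At ICC 0.15 and an assumed between-round correlation of HC effects of 0.8, the HC-by-round share is 0.15 × 0.2 = 0.03. The variance ratio is (12 × 0.03 + 0.85) / (0.03 + 0.85) = 1.375, the SE ratio 1.17 and the type I error about 9.5%.

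**The case against.** The strongest reply is that the criticised model is one reading of a short sentence in a condensed article. Random effects at HC level, in the plural, can include an HC-specific round effect. In this balanced design that alone repairs the standard error, as the simulation shows. A follow-up comparison adjusted for baseline HC values also uses both rounds, and there the HC intercept absorbs the sous-colline variance. The nesting could be set out in a statistical analysis plan that is not shown. This much stands: the article does not commit to an intercept-only model or to a difference-in-differences.

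The size is also open. All round-specific components above are assumed. The design effect implied by the sample size is about 1 + 71 × 0.0072 = 1.51 at 72 children. With no other HC variance, that leaves room for a sous-colline ICC of at most 0.51 / 11 ≈ 0.046. So 0.01 and 0.02 fit within the plan's implied figure, and 0.05 lies slightly beyond it. However, that ICC is back-solved, and the article describes the one it used only as quite high. The planned covariates, such as food security and socio-economic status, may remove part of the clustering.

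The reply does not dispose of the point. The article does choose a random-effects level, and in doing so leaves out its own second sampling stage. The ordinary reading of its sentence is an HC intercept.

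**Conclusion.** The point holds conditionally. If the two-round model has an HC random intercept alone, the standard error of the effect is too small whenever there is sous-colline or HC-by-round variance. For assumed sous-colline ICCs of 0.01 to 0.05 without HC-by-round variance, the correction factor is about 1.05 to 1.24 and the type I error about 6% to 12%. HC-by-round variance raises both; with neither component there is no error.

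Three stronger readings go too far:

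- **The planned intervals are certainly wrong.** A reader might infer this, but the text does not exclude an HC-by-round effect.
- **Power falls well below 80% because a noisy baseline is subtracted.** That needs an unconstrained difference-in-differences, which the article does not name, and a household ICC, which it does not give.
- **The sous-colline argument covers every outcome.** It covers household outcomes only, not recovery or treatment duration.

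**What to change.** State the random-effects structure of the two-round models:

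- **Household outcomes:** HC, HC-by-round, and sous-colline nested in HC and round.
- **Clinical-file outcomes:** HC and HC-by-round.
- **Alternative for either:** analyse HC-round summaries.

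Name the effect to be estimated. Because the lottery followed the baseline survey, baseline can be handled by a common baseline mean for both arms (with the random effects above) or by adjusting follow-up for baseline HC values.

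The change is to the model specification and needs no new data beyond keeping the sous-colline identifier in the household file. Its one downside is somewhat wider intervals, to the extent that round-specific clustering is present.

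### The plan permits random-effects Poisson regression for yes/no recovery; with model-based standard errors, that option would cut power from the planned 80% to about 39%

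*Protocol article*

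**What the plan says.** The quantitative part of the Protocol article (Analysis strategy plan) assesses impact with "multilevel statistical models with random effects at the HC level". Within that framework, "categorical ones (e.g. recovery yes/no) will be analysed in logistic regression or Poisson regression models". Recovery is the plan's own example. The text does not choose between the two models and does not say how Poisson standard errors would be obtained. The HC random effect is the only device it names for clustering.

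Table 3 lists recovery rates for moderate (MAM) and severe (SAM) acute malnutrition among the main outcomes at HC level. The section on sample size and randomization plans on "increasing the recovery rate of acute malnutrition in children under five years from 80 % to 90" per cent, with a 5% α-error, "a power of 80 % and an inter-cluster correlation (ICC) of 0.15", and concludes that "a minimum of 12 clinical files per HC and per nutrition service (MAM and SAM rehabilitation services) were needed". There are 45 HCs in each arm.

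**The concern.** A Poisson model sets the variance of a 0/1 outcome equal to its mean p, whereas the true variance is p(1 − p). For a rare outcome the difference is negligible. For a common one it is large, and recovery is planned at 80% to 90%.

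Clustering normally pulls the other way, and one might expect the HC random effect to bring the error back into line. It cannot do so here. A random intercept makes the counts more variable than Poisson and never less, so if the HC totals are already less variable than Poisson, its variance is estimated at zero and an ordinary Poisson model remains.

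At stake is a main outcome. Intervals would be too wide, and a true rise from 80% to 90% would more often than not be reported as not significant. The error is conservative, so it would produce missed effects and not false positives.

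**Working it through.** **Inputs, all from the Protocol article.** Recovery 80% against 90%; ICC 0.15; 12 files per HC and service; 45 HCs per arm, hence 45 × 12 = 540 files per arm and service; α 5%, taken as two-sided (the text does not say, but two-sided reproduces the stated 12 files).

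**1. The plan's own figure.** Two proportions, 80% against 90%, two-sided 5%, 80% power, no continuity correction: 199 per arm without clustering. The files per HC, m, must satisfy 45m ≥ 199 × [1 + (m − 1) × 0.15].
- m = 11: 495 against 199 × 2.50 = 497.5, not enough.
- m = 12: 540 against 199 × 2.65 = 527.4, enough.

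The stated minimum of 12 reproduces. The design effect is 2.65 and power 80.9%.

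**2. Size of the variance error.** Poisson variance over binary variance is p / [p(1 − p)] = 1/(1 − p): 5 at 80%, 10 at 90%.

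**3. Can the random effect correct it?** The variance-to-mean ratio of an HC total is (1 − p) × design effect:
- 80%: 0.20 × 2.65 = 0.53
- 90%: 0.10 × 2.65 = 0.265

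Both are below 1, so the counts are under-dispersed and there is nothing for the random intercept to absorb. With 24 files per HC (both survey rounds, or both services) at the same ICC, the ratio at 80% is 0.20 × (1 + 23 × 0.15) = 0.89, still below 1.

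**4. Standard errors of the log risk ratio.** The target is log(0.9/0.8) = 0.1178.
- Model-based Poisson: √[1/(540 × 0.8) + 1/(540 × 0.9)] = √(1/432 + 1/486) = 0.0661
- True, with clustering: √[2.65 × (0.2/0.8 + 0.1/0.9)/540] = 0.0421
- Ratio: 0.0661/0.0421 = 1.57

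**5. Power and type I error.**
- Model-based Poisson: Φ[(0.1178 − 1.96 × 0.0661)/0.0421] = Φ(−0.28) = 38.9%
- Correct standard error: Φ(0.1178/0.0421 − 1.96) = 79.9%
- Type I error of model-based Poisson at 80% in both arms: the nominal 1.96 acts as 1.96 × √(2/432)/√(2 × 2.65 × 0.25/540) = 2.69, giving 0.7%

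**6. Simulation.** 600 beta-binomial trials per scenario, with the mixed models fitted by maximum likelihood:

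| Analysis | Rejects, 80% v 90% | Rejects, 80% v 80% |
|---|---|---|
| Random-intercept Poisson, model-based SE | 38.7% | 1.2% |
| Random-intercept logistic | 84.5% | 7.3% |
| Poisson, HC-clustered robust SE | 80.5% | 6.8% |

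The Poisson random-intercept SD was estimated at about zero in every trial. Simulation error at a true 5% is √(0.05 × 0.95/600) = 0.9 points, so the null rates of the last two rows lie somewhat above nominal and their power should not be read to the last point. A separate run of 4,000 trials gave 82% power and 4.3% type I error for the robust analysis.

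**7. Sensitivity.**
- One service, ICC 0.05 to 0.36: model-based Poisson power stays between about 36% and 42%.
- MAM and SAM files pooled (24 per HC, 1,080 per arm, design effect 4.45): SEs √(1/864 + 1/972) = 0.0468 and √(4.45 × 0.3611/1080) = 0.0386, ratio 1.21; power 75% against 86%.
- Pooled at an assumed ICC of 0.25: the ratio is 0.98 and the overstatement disappears.
- Acute malnutrition near 10%: √[1/(1 − 0.1)] = 1.05, so the individual-level standard error is only about 5% too wide.

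**The case against.** The strongest reply is that the plan does not commit itself to the failing analysis. Logistic regression is named first and keeps the planned power, and so does Poisson with robust variance. The loss needs two choices that the article leaves open: Poisson over logistic, and model-based over robust standard errors. Model form and variance estimator are commonly settled in a statistical analysis plan, which is not shown. This stands against any claim that the trial, as planned, has 39% power. It does not remove the point: the article goes beyond silence by listing a model for a named outcome together with a clustering device that cannot repair it. An analyst who follows the sentence literally could arrive at the failing combination.

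A second reply is that 39% is not the power of the full analysis, which uses both survey rounds, adjusts for HC-level factors, and has HCs paired on parameters that include the percentage of recovery. That is correct. The figure describes an unadjusted follow-up comparison of one service, the same simple setting that reproduces the 12 files.

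A third is that pooling the two services shrinks the loss. It does, but the sample size is stated for each service separately.

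A reader might also infer that leaving both models open lets the effect measure (odds ratio or risk ratio) be picked after results are seen. The article does not say when the choice is made, and this is ordinary content of an analysis plan, so that inference is not supported.

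**Conclusion.** The point holds as a conditional one. The plan permits an analysis of recovery that, with model-based standard errors, defeats its own power calculation: about 39% against 80%, standard errors about 1.6 times too large, and type I error of about 1%. This rests on 12 files per HC, one service at a time, ICC 0.15, and no use of pairing, baseline or covariates. For one service it is insensitive to the ICC. With the services pooled it is smaller (75% against 86%) and can vanish at a higher ICC.

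It would be wrong to conclude that Poisson regression as such is unsuitable, or that the planned power is already lost. Robust variance or the listed logistic model avoids the problem. The concern is confined to common yes/no outcomes such as recovery and matters little for acute malnutrition near 10%.

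**What to change.** In the quantitative analysis strategy, replace the open choice for yes/no outcomes with one of two statements:

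- logistic regression with an HC random effect; or
- Poisson regression only with HC-clustered robust (sandwich) variance.

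State that random-effects Poisson with model-based standard errors will not be used for yes/no outcomes. If an analysis plan already says this, a cross-reference is enough.

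The cost is one sentence. Data, software and sample size are unchanged.
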